## 2) Based on the data from the intervention study:

- To investigate whether two key elements in the aforementioned self-cared based intervention program (the Ull Care program), PPS measurement as biofeedback marker of stress and nerve stimulation for stress reduction, may help patients with ischemic heart disease through increased self-care to:
  - Reduce chronic stress measured over a period of three months:
    - A reduction in depression and improved quality of life
    - A reduction in the stress measure PPS
    - Beneficial effect on selected cardiovascular risk factors, e.g. work of the heart, HRV, lipids
  - Over a period of 12 months to also lead to:
    - A reduction in consumption of health services
    - A positive effect on the patient's disease prognosis

## 3) Several sub studies are planned:

1. Due to the chosen randomization procedure it will be possible to perform analyses on the randomized intervention trial on the subgroups listed in section 8: age, gender, diabetes mellitus, heart failure, time from last myocardial infarction or invasive cardiological procedure. Degree of depression is listed among the main purpose, section 2.
2. Comparison of the chosen PPS measure with another and established algometer.

## 4. Design

Prospective, randomized, controlled, single-blinded study with 50 % allocation ratio for intervention. The time course of the intervention and control group is parallel. The study takes place at Herlev Hospital and is open to the following: participating patients and the instructor of the active group. The study is blinded to all others, including the statisticians who must make the main analysis. The personnel conducting the clinical examinations do not have access to the documents containing information about the treatment or treatment procedures. This is to prevent bias in the comparison between the treatment groups.

## 5. Material

### 5.1 Subjects:

The study includes 300 patients with ischemic heart disease. The patients will be recruited through the center for cardiac rehabilitation at Gentofte and Herlev Hospital respectively.

### 5.2 Inclusion criteria:

- Implemented cardiac rehabilitation program at Gentofte or Herlev Hospital minimum 6 months ago.
- Documented ischemic heart disease that qualified for a heart rehabilitation program.
- Use of aspirin, cholesterol-lowering and antihypertensive medication after Danish cardiac guidelines.
- Younger than 75 years at the time of inclusion.
- Elevated level of stress, defined as PPS  $\geq$  60.

### 5.3 Exclusion criteria

- Previously diagnosed and treated for a psychiatric disorder, except for depression.
- A chronic competing disorder that statistically is life-shortening (such as advanced cancer with metastases).
- A chronic competing disorder that is neither heart disease nor diabetes and which clearly impairs the patient's quality of life /e.g. COPD, cancer, chronic pain syndrome).

- Patients who cannot take care of themselves.
- Patients who, for various reasons, find it difficult to participate in the intervention program (e.g. language barriers).
- A scheduled cardiac surgery.
- Previous treatment with the examined active treatment.
- A change in heart medication (in terms of angina pectoris and/or heart failure) within the last month.

NB: Patients may participate in other clinical trials at the same time because this is not an exclusion criterion.

## **6. Effect variables (the intervention study)**

For the baseline study additional blood samples are taken in relation to what is mentioned in section 6.3.1 below (see point 9.3).

### **6.1 Primary effect variable:**

The degree of depression by the MDI questionnaire (Bech et al., 2001;Olsen et al., 2003)

### **6.2 Secondary effect variables:**

1. Physiological measurements of stress: Level of stress measured by PPS by the same blinded nurse (trained in PPS measurement) at baseline and after three months of observation.
2. The WHO-5 questionnaire measuring well-being (QOL) (Folker and Folker, 2008).
3. Correlation between changes in PPS and changes in MDI and WHO-5 scores respectively.

### **6.3 Tertiary effect variables:**

#### *6.3.1 Biological variables:*

1. Measure of persistent stress: serum Oxytocin, HbA1c.
2. Insulin resistance: Fasting plasma insulin, C-peptide, blood glucose (with calculation of HOMA), HbA1c, Adiponectin.
3. Chronic inflammation: Serum / plasma high sensitive CRP, Defensin, YKL-40.
4. Fat metabolism: total cholesterol, LDL and HDL cholesterol, Triglycerides.

5. Heart strain NT-proBNP and BNP.

#### *6.3.2 Physiological variables:*

1. Blood pressure, pulse, blood pressure pulse product (PRP).
2. Body Mass Index, (height and weight).
3. Body fat composition by a DEXA scan.
4. Heart rhythm variability (HRV) measured by tilt testing.

#### *6.3.3 General QOL*

1. Measured using the SF-36 questionnaire (Alonso et al., 2004; Bjorner et al., 1998).

#### *6.3.4 Health economics (cost / benefit) analysis*

Data from the last 12 months prior to the inclusion date will be used as baseline variables. This is only executed if the primary and secondary effect objectives meet the criteria for success (see paragraph 12). Data will be collected for the following services:

1. Number of visits to the practitioner (for heart problems)
2. Number of visits to a cardiologist (specialist)
3. Number of hospital visits (outpatient)
4. Number of inpatient days in a hospital

5. Use of invasive procedures (PCI and/or CABG)
6. Use of cardiovascular medicine
7. Number of sick days due to heart disease (if the person is working)

#### *6.3.5 Other variables:*

- a. Frequency of clinical event: measured by a composite endpoint when one of the following occurs: 1) visit to a hospital for a cardiac reason; 2) hospitalization of cardiac causes and 3) cardiac death. Common visits to the GP will not be counted.
- b. Patient compliance: assessed by 1) number of patients who follow the program until the end of the trial, 2) personal view of the usefulness of the program on a 7 point ordinal scale, and 3) compliance of the Ull Care program as measured by the degree of integration into daily life on a binomial scale.
- c. The number of clinical stress signs based on a designed and validated questionnaire (Ballegaard et al., 2011)
- d. Changes in medication, to ensure that any observed improvement is not due to an increase in medication prescribed by physicians outside the study protocol.
- e. Use of invasive procedures (PCI and CABG).
- f. Number of days on leave due to heart disease

## **7. Practical course (including flowchart)**

Using databases of cardiac rehabilitation patients from Gentofte and Herlev Hospital respectively approximately 600 patients with complete cardiac rehabilitation course > 6 months ago, to ensure a steady state in regard to the efficacy of the given cardiac rehabilitation, are identified. The patients are invited by letter to participate in the study.

It is expected that about 450 will accept. These are convened to an examination at Herlev Hospital Medical Department O.

All patients sign the consent form and go through the physiological preliminary examination.

Patients with PPS < 60 are ended immediately, and a subset of the first 50 patients with PPS < 45 are invited to a measuring of their body composition.

Since it is expected that 2/3 of patients have an elevated PPS measure ( $\geq 60$ ), 300 patients with PPS  $\geq 60$  are randomized to either an active or control group with 150 in each:

**Control group:** Continue their own efforts in extension of the already given cardiac rehabilitation and receive a textbook on general stress management (REHAB + CARE).

**Active group:** the same plus the Ull treatment program (REHAB + ULL).

All included patients will at baseline be offered an additional measurement of body composition.

Intervention period: 3 months.

Both the control and active group continue with the given medical treatment. If there is a change in heart condition including possible side effects of medication, the medication is adjusted according to the procedures in the rehabilitation programs at the hospital the patient is assigned to (Gentofte or Herlev Hospital). If possible, the medication should remain stable during the 3 months of the observation. The patient and the patient's own doctor are informed that the aim of the study is that any adjustment of cardiovascular medicine happen after contact with the project nurse (perhaps through a telephone hot-line).

**Control/Active group:**

1. Control group: receive a book about general stress management
2. Active group: receive in addition to the above mentioned:

Instruction in self-measurement of PPS by a PPS instructor at home. The patient is instructed in PPS measurement, nerve stimulation and the use of the web platform in order to be able to enter their own measurements. They are not instructed in stress management. There is a 45 minute home visit in the beginning plus two visits after one and two months respectively for additional technical instruction if the PPS measure is  $\geq 60$ . In addition there are 5 telephone dialogues á 15 minutes solely for technical instruction after 1, 3, 5, 6 and 10 weeks respectively. The patients receive an Ull meter, a written user's manual and an instructional DVD.

The patients record their PPS measurements either on the web platform ([www.songheart.org](http://www.songheart.org)) or on paper at least once a week

If their PPS records show a  $PPS \geq 60$  for 7 consecutive morning measurements, the patient is contacted regarding the need for additional technical instruction.

After three months of participation in the project all patients (both groups) are called to a repetition of the baseline visit at Herlev Hospital. Those who at baseline opted to have made body composition will have the same offer again if, at the physiological examination, they have lost 3 kg or more.

The two examinations at Herlev are conducted by the same blinded nurse at baseline and the 3 month follow-up respectively.

If the success criteria for the study are met, the subsequent analysis are carried out after the 12 month observation:

Use of health services over the last 12 months before the start of the study compared to the 12 months after commencement of participation.

The prevalence of clinical events. Here a Kaplan-Meier plot analysis will be used.

The Minimal Important Difference (MID) between the active and control group is set at a 10 % improvement in the active group versus the control group.

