## 7.1 Flowchart:

| Visit (number)                             | 1      | 2          | 3         | 4                                  |
|--------------------------------------------|--------|------------|-----------|------------------------------------|
| Physical location                          | Herlev | Home visit | Herlev    | Data collection via public records |
| Months                                     | 0      | 0          | 3         | 12                                 |
| Window for visits                          |        | +/-7 days  | +/-7 days |                                    |
| Informed consent                           | X      |            |           |                                    |
| Questionnaires completed                   | X      |            | X         |                                    |
| Inclusion/exclusion                        | X      |            |           |                                    |
| Blood pressure, pulse, PPS and HRV test    | X      |            | X         |                                    |
| Blood sample                               | X      |            | X         |                                    |
| Assessment of medication                   | X      |            | X         |                                    |
| Randomization                              | X      |            |           |                                    |
| Registration of clinical events            | X      |            |           | X                                  |
| Consumption of healthcare services         | X      |            |           | X                                  |
| Implementation of joint treatment          | X      |            |           |                                    |
| Implementation of active treatment         |        | X          |           |                                    |
| Measurement of body composition (subgroup) | X      |            | X         |                                    |

CONSORT Flow Chart for the SongHeart study

[figure not shown]

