## 11.2 Analysis of the effect variables

Five percent (5 %) will be used as significance level in all statistic tests.

The statistical analysis will look at two groups of cardiac patients separately: 1) those patients for whom all therapeutic approaches have been exhausted and 2) the rest. One joint analysis will be made if it is statistically reasonable. The statistics are compiled on an "intention to treat basis"; meaning that all enrolled patients are included in the subsequent analysis.

In the statistical analysis, subgroup analysis will be made for the patients with the highest PPS values: e.g. all patients with  $PPS \geq 75$ ; or for the highest quartile of PPS values.

"Closed test procedure" will be used to analyze data after 3 and 12 months in terms of the assessment of the treatment effect:

- First priority hypothesis: The Ull Care program improves the degree of depression measured by a MDI depression score, measured after 3 months of intervention.
- Second priority hypothesis: The Ull Care program improves health economic variables, measured after 12 months of intervention.
- Third priority hypothesis: The Ull Care program improves the frequency of clinical events, measured after 12 months of intervention.

Baseline measurements will be co-variant variables in relation to the applied stratification variable: the degree of depression measured by the MDI scale. Data from before and after the intervention will be analyzed separately. Delta values for

the active and control group respectively will be compared to analyze a possible treatment effect. All secondary and tertiary effect variables will be analyzed after the intervention through variance and regression analysis. If the premises for the proposed statistical analysis cannot be met, non-parametric analysis is used. Quality-of-life data will be analyzed to meet the directions of each of the questionnaires. All effect data will be presented a unifying table and primary, secondary and tertiary effect variables will be listed.

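### The 3-month DEXA scan is offered only to patients who lost 3 kg or more, so it cannot estimate the programme's effect on body fat in all randomised patients

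*Protocol*

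**What the plan says.** Protocol section 6 is headed as the effect variables of the intervention study. Within it, section 6.3.2 lists "Body fat composition by a DEXA scan" as a tertiary physiological variable, next to "Body Mass Index, (height and weight".

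Section 7 sets out when the scans are taken. For the first scan, "All included patients will at baseline be offered an additional measurement of body composition". For the second visit, "After three months of participation in the project all patients (both groups) are called to a repetition of the baseline visit at Herlev Hospital". The second scan is narrower: those who took the baseline scan "will have the same offer again if, at the physiological examination, they have lost 3 kg or more".

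The flowchart in section 7.1 marks "Measurement of body composition (subgroup" at months 0 and 3 and does not show the weight-loss condition.

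Section 11.2 covers the analysis. All tertiary variables are to be analysed after the intervention, delta values for "the active and control group respectively will be compared to analyze a possible treatment effect", and the basis is intention to treat with every enrolled patient included.

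**The concern.** A DEXA change score can exist only for a patient who has passed a weight-loss threshold measured three months after randomisation. Weight is itself a listed effect variable, it could respond to a stress-management programme, and it moves closely with fat mass. If the programme changes weight, different kinds of patients cross the threshold in the two arms, and those rescanned are no longer a randomised comparison. The rule also conflicts directly with the all-enrolled basis in section 11.2.

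What is at stake is one tertiary result. As section 11.2 stands, it would appear in the same effect table as endpoints that are due to be measured in everyone, and a real effect on fat acting through weight could be reported as close to nothing.

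**Working it through.** The protocol states no figure for this endpoint, so there is none to reproduce. The check shows what the 3 kg rule does under stated assumptions.

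**From the protocol:** repeat scan only if weight change is -3 kg or lower (section 7); 150 patients per arm (section 7); 5% significance level (section 11.2).

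**Assumed:** 3-month weight change W is normal with mean 0 in controls and mean m in the active arm, with the same SD s in both. Fat change = 0.75 × W + d + noise (SD 1 kg), where d is any direct effect on fat in the active arm. All patients accept both scans when offered. Tests are two-sided with 80% power.

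**Formulas.** With a = (-3 - m)/s:
- Fraction rescanned = Φ(a).
- Mean weight change among those rescanned = m - s × φ(a)/Φ(a).
- Apparent fat difference = 0.75 × (active mean - control mean among those rescanned) + d.
- True fat difference = 0.75 × m + d.

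**Worked case, s = 3 kg, m = -1 kg, d = 0.**
- Control: a = -1, φ = 0.2420, Φ = 0.1587, so 16% (about 24 of 150) are rescanned. Their mean weight change is -3 × 0.2420/0.1587 = -4.58 kg.
- Active: a = -0.667, φ = 0.3194, Φ = 0.2525, so 25% (about 38 of 150) are rescanned. Their mean is -1 - 3 × 0.3194/0.2525 = -4.80 kg.
- Apparent fat difference: 0.75 × (-0.22) = -0.165 kg. True difference: -0.75 kg. About 22% remains.

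**Range, d = 0.**

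| SD of weight change | Weight effect | Rescanned, control / active | True fat difference | Apparent | Remaining |
|---|---|---|---|---|---|
| 2 kg | -1 kg | 7% / 16% | -0.75 kg | -0.13 kg | 17% |
| 2 kg | -2 kg | 7% / 31% | -1.50 kg | -0.30 kg | 20% |
| 3 kg | -1 kg | 16% / 25% | -0.75 kg | -0.165 kg | 22% |
| 3 kg | -2 kg | 16% / 37% | -1.50 kg | -0.37 kg | 24% |
| 4 kg | -1 kg | 23% / 31% | -0.75 kg | -0.19 kg | 25% |
| 4 kg | -2 kg | 23% / 40% | -1.50 kg | -0.40 kg | 27% |

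A simulation with 2 million patients per arm agrees to within 0.01 kg. With d = 0 the fraction remaining does not depend on the 0.75 slope, which cancels.

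**No weight effect (m = 0).** The apparent difference equals the true one, but only 7%, 16% or 23% of patients (about 10, 24 or 34 per arm) are rescanned at SDs of 2, 3 or 4 kg. The detectable standardised difference is (1.96 + 0.84) × √(2/n): about 1.25, 0.81 or 0.68, against 0.32 with all 150 per arm.

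**Direct effect on fat (d = -0.5 kg, s = 3 kg, m = -1 kg).** Simulated apparent difference -0.66 kg against a true -1.25 kg, so about half remains.

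**The case against.** The strongest reply is that the protocol never sets out a specific DEXA comparison between arms. Body fat distribution is a stated purpose only for the baseline study (section 3, purpose 1). Purpose 2 does not name it among its cardiovascular examples, and the flowchart calls it a subgroup measurement. The between-arm comparison follows from one list item plus the general analysis wording, and a statistical analysis plan that is not shown might treat the scans descriptively. This lowers the importance of the point but does not remove it. The list is headed as the intervention study's effect variables, section 11.2 covers all tertiary variables, and no analysis plan can recover scans that were never taken.

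Three stronger readings are tempting, and the documents do not support them:
- *The comparison is simply invalid.* If the programme affects neither weight nor fat, the test among those rescanned keeps its error rate. What fails is estimation of the effect in all randomised patients.
- *Most of any real difference is lost.* That holds only for the part of a fat effect that runs through weight. In the model above, a direct effect on fat passes through the selection intact.
- *Patients who stayed stable or gained are not observed.* All are recalled at month 3, and weight/BMI is a listed effect variable. Only their second DEXA is missing.

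The calculation also concerns total fat mass. It says nothing about the size of any distortion in android/gynoid distribution.

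**Conclusion.** The point holds as a conflict between sections 6.3.2 and 11.2 on one side and section 7 on the other. DEXA scans taken under the 3 kg rule cannot give the intention-to-treat effect on body fat that section 11.2 implies. To the extent that a fat effect acts through weight it would be strongly attenuated, with about 17% to 27% remaining over the range shown. That range rests on normal weight change, no average change in controls, equal SDs and no direct effect on fat, none of which the protocol supplies.

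A reader might infer that the trial's main conclusion is at risk. It is not. DEXA lies outside the primary MDI analysis, the closed test order in section 11.2 and the success criteria in section 12, and the baseline DEXA purpose does not use the second scan. The change is worth making because it is nearly free.

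**What to change.** Reconcile sections 6.3.2, 7, 7.1 and 11.2 as follows:
- Remove body fat by DEXA from the between-arm effect variables in 6.3.2. Record this as a dated protocol change with the reason given, because section 11.1 shows that at least 60 patients were already included.
- Report the repeat scans descriptively, as changes in patients who lost 3 kg or more, without an arm comparison.
- State the weight-loss condition in the flowchart row.
- Use weight/BMI, already listed in 6.3.2, as the anthropometric effect variable.
- Leave DEXA in the baseline study as it is.

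The cost is one tertiary between-arm claim; no extra visits or measurements are needed. Making the repeat offer independent of weight change would also remove the selection. It would need additional scans, at about 0.1 mSv each by section 15, and is not needed to resolve the conflict.

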### **11.3. Cost-Utility analysis (CUA)**

A cost-utility analysis will be carried through after 12 months of intervention for comparison of active versus control treatment. Relevant data, meaning consumption of healthcare services such as hospital visits, ambulatory visits, use of medication, consumption of invasive procedures etc. will be gathered during the study. Data from SF-36 questionnaires will be used to generate OALY's based on the fact that the Minimal Important Difference (MID) in effect on physical health (PCS scale) and mental health (MCS scale) is 0,3 (calculated as shown in point 11.1) (Ware JE et al 2007). Estimations of indirect costs, such as social pensions will be included. CUA will be calculated both with and without the indirect costs.

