## 12. Success criteria

The result of the study will be concluded as positive, if the following results are reached:

Compared to the control group, the active group obtains a significant improvement in MDI depression score and with a therapeutic effect size of at least 0,4 when the effect in the active group is compared to the control group (see point 11.1 for exact calculation of the effect size).

When compared to the control group, the active group obtains a significant improvement in mean PPS measurement measured by a professional instructor and with a MID of 10 units on the PPS scale.

The patient does not experience any increased risk in connection with the intervention measured as no increase in blood pressure or serum cholesterol after treatment, Both parts are measured as mean values for the two variables in the active group when the baseline values are compared at the end of the treatment period.

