## 13. Usefulness of the study and treatment in a broader perspective

By participating in the study, each patient can get a general profit from the opportunity of an additional comprehensive health check. If the findings of the study are positive, it means that the patients in the active group have an extra benefit in terms of reduced stress, improved mood and some concrete tools for better stress management. If renewed fund applications allow it, the control group will then be offered the active treatment. The study gives the surrounding society the possibility of testing the value of a new and economically inexpensive treatment in heart patients: A treatment that is expected to have a measurable impact on the patients' future health, use of health care services and patient survival. Other scientific studies have shown that if stress and depression is reduced in a heart patient, their survival is improved. As the intervention represents a paradigm shift in the treatment of chronic illness with an emphasis on a far greater self-insight and self-effort, a positive outcome will expectedly lead to a test of the intervention in people with other chronic illnesses. The study is also designed to uncover possible links between persistent stress and heart disease and which mechanisms that is responsible for the effect that a positive outcome will show.

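### Section 7 makes the 12-month comparison of cardiac events conditional on trial success, in conflict with the flowchart and sections 3 and 11

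*Protocol*

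**What the plan says.** - **Section 7 (Control/Active group)**, after describing the 3-month visit: "If the success criteria for the study are met, the subsequent analysis are carried out after the 12 month observation". Two analyses follow. One compares service use in the 12 months before and after entry. The other reads "The prevalence of clinical events. Here a Kaplan-Meier plot analysis will be used".
- **Section 6.3.5** defines the event composite as a cardiac hospital visit, "2) hospitalization of cardiac causes and 3) cardiac death". It is listed among the tertiary variables with no condition.
- **Section 6.3.4**, on health-economic data: "This is only executed if the primary and secondary effect objectives meet the criteria for success". It points to section 12.
- **Section 12** sets three criteria. The MDI criterion is a "significant improvement in MDI depression score and with a therapeutic effect size of at least 0,4". The second is a significant PPS gain with a minimal important difference of 10 units. The third is that mean blood pressure and cholesterol do not rise in the active arm between baseline and end of treatment.
- **Section 11.2** orders MDI at 3 months, then health economics at 12 months, then events: "Third priority hypothesis: The Ull Care program improves the frequency of clinical events, measured after 12 months of intervention". It also says that every secondary and tertiary variable will be analysed.
- **Section 11.3**: "A cost-utility analysis will be carried through after 12 months of intervention for comparison of active versus control treatment".
- **Flowchart (7.1) and section 3.** The flowchart marks event registration and service use at visit 4 (month 12, public records). Section 3 names 12-month service use and prognosis among the study's purposes. Neither carries a condition.
- **Section 13**, after describing a positive result: "If renewed fund applications allow it, the control group will then be offered the active treatment". No timing is given.

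**The concern.** Whether a randomised comparison of cardiac events is made should not depend on how the 3-month outcomes turned out. Under section 7 it does. A trial that misses any success criterion loses its planned 12-month event comparison, so that comparison would appear only alongside a favourable main result.

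The third criterion makes this worse. A rise in mean blood pressure or cholesterol in the active arm is itself a failure. A possible safety signal at 3 months would therefore switch off the analysis best placed to follow it up, in a trial whose summary and section 15 call the intervention risk-free.

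The sections also disagree on what must be true before the 12-month analyses are run. Whoever carries them out would have to choose after seeing the 3-month data.

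**Working it through.** **1. The plan's own figure.** No figure is given for the 12-month event analysis. Section 11.1 gives the sample size: difference 5, SD 9, alpha 5% (two-sided assumed, since sidedness is not stated), power 80%.

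n per group = 2 × (1.96 + 0.8416)² × 9² / 5² = 50.9, so 51 against 50 stated; power at 50 is 79.3%. With 36% prevalence, 100 / 0.36 = 278. A 10% margin gives 306 (× 1.1) or 309 (/ 0.9) against 300 stated. The figure reproduces to within 3%, and 150 per arm is used below.

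**2. MDI criterion alone.** Section 11.1 takes the effect size over all included patients. By normal approximation its standard error is √(2/150) = 0.1155. Significance needs an observed value of at least 1.96 × 0.1155 = 0.226, so the 0.4 floor is the binding part:

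P(criterion met) = 1 − Φ((0.4 − δ) / 0.1155)

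| True effect δ | (0.4 − δ)/0.1155 | Met | Analysis dropped | MDI significant | Significant but below 0.4 |
|---|---|---|---|---|---|
| 0 | 3.46 | 0.0003 | 99.97% | 2.5% | 2.5% |
| 0.3 | 0.87 | 0.193 | 81% | 73.8% | 54.5% |
| 0.4 | 0 | 0.500 | 50% | 93.4% | 43.4% |
| 5/9 | −1.35 | 0.911 | 9% | 99.8% | 8.7% |

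In the last column the section 11.2 order moves on to the 12-month steps while section 7 stops. With only 50 per arm, the analysis is dropped in 98%, 69%, 50% and 22% of trials respectively.

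**3. Adding blood pressure and cholesterol.** Section 12 does not say whether any rise in an observed mean counts as failure. Assume that it does, that the true changes are zero, and that they are independent of MDI. Each mean then avoids a rise with probability 0.5. Both avoid it with probability 0.25 if the two are independent, or 0.5 if they are perfectly correlated.

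- At δ = 0.4: 0.50 × 0.25 = 0.125 to 0.50 × 0.5 = 0.25.
- At δ = 5/9: 0.911 × 0.25 = 0.228 to 0.911 × 0.5 = 0.456.

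The PPS criterion cannot be added, because no SD of the 3-month PPS change in this setting is given. It can only lower these figures.

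**4. Could the lost comparison show anything?** The protocol gives no event rate. Assuming 12-month control rates of 5%, 10%, 20% and 30%, power at 150 per arm to detect a doubling (two-proportion normal approximation) is 38%, 68%, 97% and nearly 100%. At the higher rates harm of that size would probably be seen.

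**5. The conditions side by side.**

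| Place | Condition for the 12-month analysis |
|---|---|
| Section 7 | All of section 12; service use and events are then released together |
| Section 6.3.4 | Economic data only; primary and secondary objectives, by reference to section 12 |
| Section 11.2, priority order | MDI, then economics, then events; no effect-size floor, PPS or blood pressure/cholesterol condition |
| Section 11.2, tertiary variables | None |
| Section 11.3 | None |
| Flowchart, section 3, section 6.3.5 | None |

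Section 6.3.4 is itself unclear. Section 12 omits two of the secondary variables in section 6.2 (WHO-5 and the correlations), while its third criterion uses variables that section 6.3 lists as tertiary. These passages cannot all be followed.

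**The case against.** The strongest reply is that much of the protocol carries no such condition. Events are registered at month 12 for everyone, section 11.2 says that all tertiary variables will be analysed, and section 17 commits to publishing negative as well as positive results. This stands. A reader might infer that harm in a failed trial would never be examined, or that selective reporting is designed in. The documents do not support that: they conflict, and section 7 is the passage that drops the analysis.

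A reader might also take the event composite as the only clinical outcome and the only check on the risk-free claim. It is neither. Section 6.3.5 also lists invasive procedures and medication changes, and section 6.3 lists NT-proBNP, lipids, blood pressure and pulse. The third success criterion is assessed in every trial. But that criterion is a before-after comparison within the active arm on two markers at 3 months. It does not replace a randomised comparison of events at 12 months.

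Nor does section 7 strictly contradict the closed test procedure. An ordered procedure is itself a condition on later claims, and section 7 includes a significant MDI result. The two simply differ. Section 11.2 also places events after health economics, not after MDI alone.

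Section 6.3.4 restricts only the economic data, and making a cost analysis depend on efficacy is a defensible use of resources.

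On size, a true effect of exactly 0.4 with no change in blood pressure or cholesterol is one scenario. The planning values give 5/9, although section 11.1 sized the trial on patients with MDI of at least 20 and takes the effect size over all patients. Section 1.6 reports earlier effects of 10% on blood pressure and 13% on cholesterol in office workers. The combined range of 12.5% to 25% is therefore illustrative and not a bound.

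Finally, the offer to controls in section 13 depends on new funding and has no stated timing. A clash with the 12-month comparison is possible but not shown.

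**Conclusion.** The concern holds as a conflict within the protocol that has a real consequence. If section 7 is followed, the planned randomised comparison of cardiac events, including cardiac death, is not made in a failed trial, even when the failure was a rise in a cardiac risk marker in the active arm.

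The condition is no formality. The MDI criterion alone would drop the analysis in about half of trials at the protocol's own minimal important effect of 0.4, and in nearly all trials with no effect; at 5/9 the figure is 9%. At 0.4, sections 7 and 11.2 give different instructions in about 43% of trials. These figures assume 150 per arm, complete data, a two-sided 5% test and a normal approximation.

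The lower chances of 12.5% to 25% that the analysis is run at 0.4 rest on the further assumptions in step 3 and leave out PPS.

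**What to change.** - In section 7, remove the success condition for clinical events. State that 12-month events will be reported by randomised arm, with 95% confidence intervals, for all randomised patients whatever the 3-month result.
- Use the section 11.2 order only to decide which 12-month efficacy results may be claimed as confirmatory.
- Align sections 6.3.4, 7, 11.2, 11.3 and 12 on one stated condition. Whether the cost analysis stays conditional is the sponsor's choice, but sections 6.3.4 and 11.3 must agree.
- Reconcile the possible offer to controls in section 13 with the 12-month comparison, and analyse patients as randomised.

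The cost is one small extra analysis of register data already scheduled at visit 4, and edits to several sections. No additional visit is needed.
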